
## Blinding

Blinding of the researchers is being tested for feasibility to see whether it would be possible in the definitive trial. Researchers record instances where they believe they have been unblinded in any way.

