The researcher delivers the baseline data collection assessment using the narrative conversational format developed in our previous studies.^7^ The questions from the WEMWBS (the primary outcome) are read out to participants in a precise and consistent manner should the participant prefer/require this rather than completing it themselves (method of completion is recorded). Questions from other measures are incorporated into a specially constructed flexible script that avoids duplication of subject matter to minimise disengagement or irritability. As per the consent process, individuals who lack capacity on a particular day will be given additional opportunities to complete the baseline data collection assessment, before being deemed to be ineligible to continue participation in the study. This is a particularly important allowance when the population of interest often live challenging lives with competing priorities.

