## Confidentiality

### Randomisation

Allocation to intervention or control group uses minimisation, with a random element, to ensure balance between treatment arms with respect to age, gender and recruitment site. Recruitment site is determined by a combination of geographic region and the service type: (1) Northwest CRC; (2) Southwest CRC; and (3) Southwest NPS. Allocation is achieved by means of a web-based system created and maintained by the Peninsula Clinical Trials Unit.

Once the participant has completed the screening interview and baseline data collection assessment, the researcher/administrator accesses the randomisation website using a unique username and password. The website requires entry of the study site, participant’s initials, participant’ s date of birth and gender, before returning the participant’s unique randomisation number and allocation (intervention or control) to the trial administrator via email. The website confirms that the allocation process has been successful but does not display the participant’s allocated group at the point of entry to maintain blinding of the research assistants (RAs). The first participant was randomised on 18 October 2016.

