### Outcome measurement

#### Feasibility outcomes

The study aims to collect data on the following acceptability and feasibility outcomes: proportion of eligible participants; recruitment rates; rates of attrition and loss to follow-up; completion and completeness of data collection; estimates of the distribution of outcome measures; acceptability of intervention to participants; and acceptability of study participation to participants.

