#### Data collection

The mixed methods data collection will include:

Face-to-face semistructured interviews will be conducted with:STRENGTHEN HTs (n=6) across both geographical regions.CRC and NPS staff (n=6) across both geographic regions.Participants who disengaged before an agreed end (up to 6).Participants randomised to the intervention arm of the pilot (high and low levels of engagement) (n=6).Participants randomised to the control arm of the pilot (n=6).

All interviews will be digitally audio-recorded and transcribed verbatim.

We will also collect:Field notes, written by RAs, on potential participants reasons for declining to participate in the study, while being sensitive to their rights to decline further participation without providing a reason.Digital audio recordings of HT sessions (n=20). Consent to record sessions will be sought at the start of the intervention and reconfirmed at each session prior to recording.HT session report forms. HTs will keep a record of each session, including information on: date, location, duration, type (face to face or by telephone), subsidy use, primary goals of the participant, goals met (if applicable) and any difficulties encountered for discussion in supervision.

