### Statistical analysis

#### Quantitative

An initial analysis after 6-month follow-up is completed will focus on (1) recruitment and retention; and (2) adherence to the intervention:A Consolidated Standards of Reporting Trials (CONSORT) diagram will provide a detailed description of numbers approached, meeting eligibility, having baseline data collected, being randomised and having follow-up data collected.A descriptive analysis will report on the proportions of those randomised to the intervention and who attended two or more sessions, completed all sessions and set behaviour change goals in personal plans.

Data from screening, recruitment and follow-up logs will be used to generate realistic estimates of eligibility, recruitment, consent and follow-up rates in the study population to assess the feasibility outcomes of the study. We will also estimate completion rates for each of the proposed outcome measures at each time-point. All such estimates will be accompanied by appropriate confidence intervals to allow conservative assumptions to be made in the planning of the definitive trial. Individuals lost to follow-up will be compared with those who complete the pilot study to identify any potential bias.

It is inappropriate to use pilot study data to formally test treatment effects, therefore the statistical analyses will be of a descriptive nature.^42 43^ We will follow the CONSORT extension for reporting of pilot and feasibility studies^43–45^ and take note of the CONSORT extension for reporting of patient-reported outcomes.^46^ Descriptive statistics of the proposed primary and secondary outcomes will be produced, as appropriate for each measure for each group. Interval estimates of the potential intervention effects, relative to usual care, will be produced in the form of a 95% CI to ensure that the effect size subsequently chosen for powering the definitive trial is plausible, but no formal hypothesis testing will be undertaken of the pilot data.^42^ Analyses will be on an intention-to-treat basis.

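### Researcher blinding is tested only through a record of believed unblinding, which gives a lower bound, and blinding is missing from the listed feasibility outcomes

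*Protocol article*

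**What the plan says.** The Blinding section of the protocol article states an aim: "Blinding of the researchers is being tested for feasibility to see whether it would be possible in the definitive trial". It then gives one method: "Researchers record instances where they believe they have been unblinded in any way". The Randomisation section adds a safeguard, in that the website does not show the allocated group to the person entering the data. That protects blinding at the start but does not measure whether it lasts.

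The Feasibility outcomes section lists seven items. It begins with "proportion of eligible participants; recruitment rates; rates of attrition and loss to follow-up; completion and completeness of data collection" and goes on to outcome distributions, acceptability of the intervention and acceptability of taking part. None concerns blinding.

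The Quantitative part of the statistical analysis section names no summary of unblinding. It does provide for counts of assessments: "Data from screening, recruitment and follow-up logs will be used to generate realistic estimates of eligibility, recruitment, consent and follow-up rates", and "We will also estimate completion rates for each of the proposed outcome measures at each time-point".

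**The concern.** The record is one-sided. As worded, it calls for an entry when a researcher believes that blinding was broken, and for nothing when the researcher believes it held. Silence therefore has at least three meanings: the researcher is still blind, an entry was forgotten, or the researcher came to suspect the arm gradually without any single event to write down.

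The third is plausible from the article's own design. Follow-up asks about action planning, self-monitoring and social support, which the health trainer works on. The resource-use questionnaire is administered by an interviewer. Sessions run over 14 weeks, so the 3-month visit, at about 13 weeks, can fall while they continue. In a control participant the cue is that nothing of the kind is mentioned, and that is not naturally an event.

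Nor does the article describe recording which arm the researcher believes the participant is in, so a correct belief cannot be told from a wrong one.

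At stake is a question that the pilot set for itself. If a short log is read as evidence that blinding held, the definitive trial may be planned on an unproven claim of blinded assessment, with a self-reported scale as its proposed primary outcome.

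**Working it through.** The article gives no figure on blinding, so there is none to reproduce. The calculation shows what the record can and cannot establish.

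**Inputs**
- Target of 120 participants (Sample size), allocated 1:1 (Study design): 120 / 2 = 60 per arm.
- Minimum with follow-up data for estimating an SD: 70, or 35 per group (Sample size); 2 × 35 = 70 agrees.
- Two follow-up assessments per participant, at 3 and 6 months (inclusion criteria and Table 1).
- Probability that recognised unblinding is recorded: not in the article. Values of 1, 0.75 and 0.5 are assumed.

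**Step 1: the denominator.** Each visit has at most 60 assessments per arm, so at most 60 × 2 = 120 per arm over both visits. At the stated minimum it is 35 per arm per visit. The follow-up logs and completion rates will give the actual numbers.

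**Step 2: what the record gives.** With x entries among n assessments, p = x/n and z = 1.96, the Wilson 95% interval is

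[p + z²/(2n) ± z·√(p(1−p)/n + z²/(4n²))] / (1 + z²/n).

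- 12 of 60: 20%, interval 11.8% to 31.8%.
- 7 of 35: 20%, interval 10.0% to 35.9%.

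These describe logged unblinding, and they treat assessments as independent. Visits by one researcher may be correlated, which would widen them.

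**Step 3: what the record cannot give.** Let u be the true proportion of assessments with recognised unblinding and r the probability that it is recorded. The logged proportion is u × r.
- u = 20%, r = 1: 0.20 × 60 = 12 entries.
- u = 40%, r = 0.5: 0.40 × 0.5 × 60 = 12 entries.
- u = 40%, r = 0.75: 0.40 × 0.75 × 60 = 18 entries.
- u = 60%, r = 0.5: 0.60 × 0.5 × 60 = 18 entries.

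The same count arises from quite different truths. With nothing assumed about r, 12 entries leave 60 − 12 = 48 assessments of unknown status, so u lies anywhere from 12/60 = 20% to 60/60 = 100%. The sampling interval in step 2 does not cover this uncertainty.

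**Step 4: what a required item would give.** Every completed assessment then has a status. The widest intervals, near 50%, are:
- 30 of 60: 37.7% to 62.3%.
- 18 of 35 (51.4%): 35.6% to 67.0%.

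These are best cases, because only assessments still to come can carry the item. Trial status gives 7 December 2017 as the last recruitment and June 2018 as the planned end of follow-up. The number of visits outstanding is not stated.

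**The case against.** The strongest reply is that this is a condensed article. It points to a full protocol in a supplementary file that is not shown, and the form, timing and tabulation of the record may be set out there. That stands, and no missing detail of that kind is held against the plan. The point concerns the method the article does state, and an aim in one section that has no counterpart in the outcome list of another.

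A second reply is that the record covers unblinding *in any way*, so a researcher who infers the arm should make an entry. This is fair and narrows the gap. It does not give meaning to an assessment without an entry.

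Third, the pilot is descriptive and tests no hypothesis. True, and it keeps the point modest. But feasibility is what the pilot exists to assess, and blinding is one of the things it says it is testing.

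Fourth, a required item is still self-report, and some guesses will be right by chance. Also true: the item removes the ambiguity of silence, not every error.

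A reader might go further and infer any of the following. The article supports none of them.
- *The record is optional.* It says only that researchers make it.
- *There is no denominator.* The follow-up logs and completion rates supply one.
- *Nothing can be learnt by arm.* Allocation is held in the randomisation system, so entries can be tabulated by arm.

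**Conclusion.** The point holds in a limited form. The method described yields a lower bound on unblinding that researchers recognised, by arm and by visit. It cannot confirm that blinding held where nothing was entered. Because the believed arm is not described as recorded, the bound concerns belief and not correct knowledge of allocation. The omission of blinding from the feasibility outcomes is a plain inconsistency with the Blinding section.

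The size of any shortfall cannot be estimated from the article. The doubling from 20% to 40% rests on an assumed recording rate of one half and is only an illustration.

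Two further inferences should not be drawn. The first is that knowledge of allocation biased WEMWBS because items "are read out to participants in a precise and consistent manner should the participant prefer/require this". That sentence describes baseline collection, which precedes randomisation, so carrying it over to follow-up is conjecture. The second is that process interviews unblind the outcome assessors. The article does not say who interviews participants or when. Neither supports a change to the plan.

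**What to change.** - At every remaining 3- and 6-month assessment, have the researcher complete one required item after WEMWBS: allocation known; thinks intervention; thinks control; no idea. Ask for the reason.
- Report the item by arm and visit, over completed assessments, with 95% CIs, keeping known allocation apart from guesses.
- Add unblinding of researchers to the listed feasibility outcomes.
- For visits already completed, report the existing record by arm over the number of assessments held, and label it a lower bound on recognised unblinding.

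The cost is one tick-box with a reason field per assessment, and one table. Guesses may reflect perceived benefit or chance, which is why the reason is needed and why guesses are kept separate. Completed visits will lack the item. If follow-up has already closed, only the last two changes can be made in this pilot.

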### Outcome measurement

#### Feasibility outcomes

The study aims to collect data on the following acceptability and feasibility outcomes: proportion of eligible participants; recruitment rates; rates of attrition and loss to follow-up; completion and completeness of data collection; estimates of the distribution of outcome measures; acceptability of intervention to participants; and acceptability of study participation to participants.

#### Assessments

Data are collected in the following areas as proposed outcome measures to be used in a future definitive trial and to assist with predicting SD size for future sample size calculations: subjective mental well-being (WEMWBS)^20 21 33 34^; self-reported smoking (number of cigarettes smoked per day)^27^; Fagerström Test for Cigarette Dependence^35^; alcohol use Alcohol Use Disorder Identification test (AUDIT-C)^36^; diet (Dietary Instrument for Nutrition Education)^37^; physical activity (7-day recall of physical activity)^38^; substance use Treatment Outcomes Profile (TOPS)^39^; confidence, importance, access to social support, action planning and self-monitoring measures relating to the four health behaviours; health-related quality of life (EQ-5D-5L and SF-36); and health, social care, criminal justice and voluntary sector resource use (see table 1).

**Table 1 T1:** SPIRIT table study schedule

		Baseline assessment				
		Screening	Baseline data	Allocation		
Timepoint		***t_1_***	***t_1_***		***+3 months*** ***T_2_***	***+6 months*** ***T_3_***
Enrolment:						
Eligibility screen		X				
Informed consent		X				
Allocation				X		
Interventions:						
Intervention group:	Strengthen intervention					
	Usual care					
Control group:	Usual care					
Assessments:						
Demographics			X			
WEMWBS			X		X	X
AUDIT-C			X		X	X
DINE			X		X	X
7-day PA recall			X		X	X
Self-reported smoking			X		X	X
FTCD			X		X	X
Importance, confidence, social support, action planning and self-monitoring			X		X	X
Treatment Outcomes Profile			X		X	X
EQ-5D-5L Questionnaire			X		X	X
SF-36			X		X	X
Resource use questionnaire			X		X	X
Safety monitoring:						
Adverse event reporting						

AUDIT-C, Alcohol Use Disorder Identification Test; DINE, Dietary Instrument for Nutrition Education; FTCD, Fagerström Test for Cigarette Dependence; PA, physical activity; SF-36, 36-Item Short Form Survey; WEMWBS, Warwick and Edinburgh Mental Wellbeing Scale.

## Data collection

### Process evaluation

A parallel process evaluation is taking place alongside the pilot trial.

#### Aims

The aims of the process evaluation are: (1) to assess whether the intervention is being delivered as per manual and training; (2) to ascertain components of the intervention that are critical to delivery; (3) to explore reasons for divergence from delivery of intervention as manualised; (4) to understand when context is moderating delivery; (5) to understand the experience and motivation of participants in the control arm of the pilot to maximise retention in a full trial; (6) to explore reasons for declining to participate in the trial; (7) to explore reasons for disengaging in the intervention before an agreed end; and (8) to understand, from a participant perspective, the benefits and disadvantages of taking part in the intervention.

#### Data collection

The mixed methods data collection will include:

Face-to-face semistructured interviews will be conducted with:STRENGTHEN HTs (n=6) across both geographical regions.CRC and NPS staff (n=6) across both geographic regions.Participants who disengaged before an agreed end (up to 6).Participants randomised to the intervention arm of the pilot (high and low levels of engagement) (n=6).Participants randomised to the control arm of the pilot (n=6).

All interviews will be digitally audio-recorded and transcribed verbatim.

We will also collect:Field notes, written by RAs, on potential participants reasons for declining to participate in the study, while being sensitive to their rights to decline further participation without providing a reason.Digital audio recordings of HT sessions (n=20). Consent to record sessions will be sought at the start of the intervention and reconfirmed at each session prior to recording.HT session report forms. HTs will keep a record of each session, including information on: date, location, duration, type (face to face or by telephone), subsidy use, primary goals of the participant, goals met (if applicable) and any difficulties encountered for discussion in supervision.

#### Analysis

Intervention fidelity will be assessed through the scoring of audio recordings of HT sessions against a developed list of six key intervention processes: (1) active participant involvement; (2) motivation building for changing a behaviour and improving mental well-being; (3) set goals and discuss strategies to make changes; (4) review efforts to make changes/problem solving; (5) integration of concepts;and (6) engaging social support. These will be scored on two domains: practitioner adherence to the protocol and competence of delivery.

Quantitative data will be summarised descriptively, with CIs as appropriate. Any factors that are identified as possibly contributing to participants’ intervention engagement and trial recruitment and retention will be explored in more detail in the qualitative data. Data from the qualitative sources (eg, interviews and audio recordings) will be synthesised into a Framework Analysis grid supported by NVivo 10 software.^40^ The deductively driven components of the framework analysis will explore the feasibility and acceptability of the intervention and the research data collection techniques. Quantitative and qualitative data will also be compiled into case studies for a purposively selected subsample of participants to maximise understanding of how the intervention is, or is not, working for individuals.^41^ Any procedures that need to be adapted will be identified and improvements, and solutions will be identified. The size and impact of potential changes will inform a decision as to whether this is an internal or an external pilot trial prior to progression to a definitive trial.

#### Contribution

The process evaluation will contribute to the research through: (1) revision of the logic model of how we understand the intervention to work, development of the way in which we deliver the intervention and how we should optimise research data collection in a definitive trial; (2) identification of which areas of the intervention are not being delivered as intended to help plan for future training and development in a definitive trial; (3) generalisable learning about the feasibility and acceptability of trial procedures with this population; (4) the decision as to whether to progress to a full trial or not; and (5) the design of the process evaluation for a full trial.

### Statistical analysis

#### Quantitative

An initial analysis after 6-month follow-up is completed will focus on (1) recruitment and retention; and (2) adherence to the intervention:A Consolidated Standards of Reporting Trials (CONSORT) diagram will provide a detailed description of numbers approached, meeting eligibility, having baseline data collected, being randomised and having follow-up data collected.A descriptive analysis will report on the proportions of those randomised to the intervention and who attended two or more sessions, completed all sessions and set behaviour change goals in personal plans.

Data from screening, recruitment and follow-up logs will be used to generate realistic estimates of eligibility, recruitment, consent and follow-up rates in the study population to assess the feasibility outcomes of the study. We will also estimate completion rates for each of the proposed outcome measures at each time-point. All such estimates will be accompanied by appropriate confidence intervals to allow conservative assumptions to be made in the planning of the definitive trial. Individuals lost to follow-up will be compared with those who complete the pilot study to identify any potential bias.

It is inappropriate to use pilot study data to formally test treatment effects, therefore the statistical analyses will be of a descriptive nature.^42 43^ We will follow the CONSORT extension for reporting of pilot and feasibility studies^43–45^ and take note of the CONSORT extension for reporting of patient-reported outcomes.^46^ Descriptive statistics of the proposed primary and secondary outcomes will be produced, as appropriate for each measure for each group. Interval estimates of the potential intervention effects, relative to usual care, will be produced in the form of a 95% CI to ensure that the effect size subsequently chosen for powering the definitive trial is plausible, but no formal hypothesis testing will be undertaken of the pilot data.^42^ Analyses will be on an intention-to-treat basis.

#### Economic analysis

The pilot study will be used to estimate the resource use and costs associated with the delivery of the intervention and to develop a framework for estimating the cost-effectiveness of the STRENGTHEN intervention plus usual care, versus usual care alone, in a future economic evaluation alongside a fully powered RCT. We will develop and test economic evaluation methods for the collection of resource use data, and for estimating related costs, and pilot the collection of outcome data appropriate for economic evaluation. In a future full economic evaluation, it is anticipated that the primary perspective for analyses will be that of the National Health Service (NHS) and Social Care Services (ie, third-party payer), with a broader participant and societal perspective explored in sensitivity analyses, and this will guide the development of the methodological framework in the pilot study.

The key areas of resource use and costs associated with the delivery of the intervention will be identified (eg, HT time, training, supervision, travel and consumables), and methods will be tested for the collection of these data. This will be via within-trial participant level records of HT input (including contact time and non-contact time). Data on participant health service use, social care service use and other broader aspects of resource use will be collected using self-report (interviewer administered) questionnaires at baseline, 3-month and 6-month follow-ups. This resource use questionnaire will be developed specifically for this participant population, using the approach described for the Client Service Receipt Inventory^47^, and based on our experience of collecting resource use data in a wide range of prior studies.

A future full economic evaluation will present the cost-effectiveness analysis with the incremental cost per unit of change on the primary outcome measure (expected to be the WEMWBS). The primary economic endpoint of policy relevance will be the incremental cost per quality-adjusted life year (QALY) gained. QALYs will be estimated using participants’ data collected using the EQ-5D-5L^48^ and the recommended value set for England.^49^ Given uncertainty associated with estimating QALYs for this population, the SF-36, from which the SF-6D can be derived,^50^ will also be used to estimate QALYs in sensitivity analysis. EQ-5D-5L and SF-36 data are collected at baseline, 3-month and 6-month follow-ups, and the pilot study will assess the feasibility of use and completion rates regarding these measures.

A future economic evaluation is expected to include extrapolation from the trial outcomes to extend the trial-based cost-effectiveness analysis over the longer term, for example, using 1-year and 2-year time horizons. Such mathematical modelling would involve evidence synthesis and the use of assumptions, and the pilot study will be used to consider these issues in the context of future research. In addition, the pilot study data will be described in a cost-consequences framework, which presents costs and outcomes in a disaggregated, tabular format.^51 52^

